### Patient recruitment and accrual

Patient enrollment commenced on August 19, 2022, and is expected to be completed in 2 years, likely by August 2024. Potential research participants are identified by the institutional clinical trials staff, the clinical investigator, or a member of the patient’s management team. In cases where the investigator is a member of the treatment team, they review the electronic medical records to determine if a patient may be a suitable participant for the PROMISSED trial. Potential participants contacted by their treating clinician are referred to the principal or sub-investigator or the clinical trials staff. The principal investigator (PI) may also perform chart review for patients with whom they do not have a therapeutic relationship for the limited purpose of identifying eligible patients for the current trial—in such cases, patient contact information is recorded, and these patients are approached later regarding potential enrollment in the PROMISSED trial. During the process where eligible patients are identified for potential participation, the patient may be asked to provide specific health information that is required for the recruitment and enrollment process. The investigator/trials staff may also review parts of their electronic medical records to determine eligibility. For most of the potential participants, the initial contact between research staff and the prospective participant is through either the treatment team, the PI, or the clinical trials staff working in tandem with the treatment team. The recruitment process discussed above presents no more than minimal risk to the privacy of the individuals undergoing screening. Only reasonable and minimal protected health information (PHI) is maintained as part of a screening log.

Once potential participants are identified, definitive eligibility is confirmed as per the inclusion and exclusion criteria specified previously. Informed consent for participation in the trial is obtained by a credentialed study investigator. During the enrollment process, registering staff complete a study-specific eligibility checklist. The staff member who signs the eligibility checklist confirms whether a participant is eligible for study enrollment.

### Randomization, blinding, and allocation concealment

Participants are randomized to either the standard of care (arm 1) or early, upfront RT plus standard of care (arm 2). At the time of randomization, clinicians fill out the Lesion Identification Worksheet (Supplementary file 2: Appendix 2) to document the ≤ 5 high-risk spine metastases per protocol definition to be followed during the protocol in both arms. Once the participant’s eligibility is established, the registration is finalized, and the participants are randomized by the statistician for the study. Randomization is accomplished by the method of a random permuted block and stratified by disease histology (breast and prostate vs. other solid tumors) and planned standard of care treatment (observation vs. systemic therapy). After the treatment arm is determined by randomization, the research coordinator notifies the investigator of the treatment arm within 24 h of randomization. We employ allocation concealment by hiding the allocation sequence from which participants are assigned to the groups until the assignment to prevent selection bias. Both the treating physician and the participant are informed about the treatment they are receiving.

### Study interventions

All participants in the current study receive systemic therapy as per the standard of care, while arm 2 also receives RT. The specifics of RT, target volume, and organ-at-risk delineation and plan evaluation is performed according to institutional standards. For this protocol, total dose and dose fractionation may be delivered at the discretion of the treating radiation oncologist. All techniques, including conventional, 3D conformal RT (3D-CRT), intensity-modulated RT (IMRT), or SRS techniques may be used, with or without image guidance, as deemed appropriate.

Participants undergo RT to each lesion using one of the dose and fractionation regimens presented in Table 1. A variety of dose fractionation schedules including conventional palliative doses as well as SRS schedules are allowed per protocol. After using appropriate immobilization, a simulation is captured for all participants followed by conduct of a CT or MR imaging in the treatment position. The radiation oncologist determines the utilization, if any, of oral or intravenous contrast.

**Table 1 Tab1:** Dose and fractionation of radiotherapy in the PROMISSED trial

Total dose	Fractions	Dose per fraction	Verification
2000 cGy	5	400 cGy	MV or KV or MR
3000 cGy	10	300 cGy	MV or KV or MR
3000 cGy	5	600 cGy	KV and CBCT or MR
2400 cGy	3	800 cGy	KV and CBCT or MR
2700 cGy	3	900 cGy	KV and CBCT or MR
2400 cGy	2	1200 cGy	KV and CBCT or MR

Supportive strategies for optimal medical care, including medications for acute RT reactions, are given during the trial at the discretion of the treating physician(s) in bounds of the protocol. These supportive therapies are formally documented as concomitant drugs. Any systemic therapies, such as hormone therapy, chemotherapy, immunotherapy, or targeted therapies, may be given based on the treating physician’s discretion. Pain management in order to help the participant come in position for the RT, but not for long-term control, is allowed to reduce voluntary movement. Opioid pain medications may be used, or their use increased, for positioning study participants for RT as required; however, the participants need to return to the baseline level of pain management after completion of RT. Drugs such as alprazolam are permitted if absolutely required to alleviate the participants’ anxiety or for treatment immobilization purposes. Per-protocol treatment is stopped when there is a systemic or local disease progression leading to enrollment in hospice. If any participants lack the ability or resources to get follow-up CT/MR scans or clinical evaluation, this information is recorded.

### Discontinuation of study intervention

Early discontinuation is considered for a patient based on the patient’s and treating physician’s decision for standard of care therapies. Protocol treatment is discontinued when there is systemic or local progression of disease resulting in hospice enrollment.

### Schedule of assessments

The full schedule of assessments is described in Table 2. All included participants have objective confirmation of metastatic disease through either standard of care biopsy of a metastatic lesion or a radiology review documenting metastatic disease. Within 8 weeks (56 days) of trial entry, all participants will have had a (1) FDG-PET/CT scan or CT of the chest, abdomen, and pelvis; (2) MRI of the spine with and without contrast; (3) full medical history including comorbidities, current medications, and performance status; and (4) physical exam including vital signs (O_2_ saturation, blood pressure, heart rate, respiratory rate, and temperature), weight, and height. Following randomization, all participants in both study arms are scheduled for follow-up at 1 month (± 2 weeks), 3 months (± 4 weeks), 6 months (± 8 weeks), 12 months (± 12 weeks), and 24 months (± 16 weeks) and receive the following assessments: clinical evaluation, assessment of performance status, imaging studies, evaluation of AE (CTCAE v5.0) for individuals in arm 2, BPI Short Form, and EQ-5D (Table 3).

**Table 2 Tab2:** Schedule of assessments in the PROMISSED trial

Assessments*	Pre-enrollment	Baseline	Treatment	1-month F/U^1^	3-month F/U^1^	6-month F/U^1^	12-month F/U^1^	24-month F/U^1^
Informed consent	X							
Eligibility verification	X							
Physical exam	X^2^				X	X	X	X
Medical history	X^2^							
Performance status		X^3^			X	X	X	X
Skeletal related events (SREs)^4^								
Lesion identification worksheet^5^		X						
Numeric pain rating scale (NPRS)	X^6^		X^8^	X^9^	X	X	X	X
Neurological exam	X^6^				X	X	X	X
Imaging of the spine (MRI preferred, acceptable alternates include CT scan or bone scan)	X^7^				X	X	X	X
Documentation of patient’s pain medication^10^	X^6^							
BPI (QL)^11^		X			X	X	X	X
FACT-G (FA)^12^		X			X	X	X	X
EQ-5D (HP)^13^		X			X	X	X	X
Adverse event (AE) evaluation			X	X	X	X	X	X

*All the assessments will come from randomization. Therefore, both arms (arms 1 and 2) have the same timelines

^1^From randomization (times will be the same for intervention and without intervention) treatment. The window for the follow-up visits will be (1) 1 month ± 2 weeks; (2) 3 months ± 1 month; (3) 6 months ± 2 months; (4) 12 months ± 3 months; (5) 24 months ± 4 months

^2^Within 4 weeks before registration. Registration is considered when the eligibility is signed by the investigator

^3^Performance status can be collected before consent

^4^Performed at any point that the patient meets any of the criteria for the protocol-defined SRE

^5^See Supplementary file 2: Appendix 2: Lesion Identification Worksheet

^6^Within 1 week before registration. Please see Supplementary file 2: Appendix 3: Numeric pain rating scale (NPRS) and Supplementary file 2: Appendix 4: Neurological exam. Registration is considered when the eligibility is signed by the investigator

^7^Within 6 weeks before registration. Registration is considered when the eligibility is signed by the investigator

^8^NPRS is collected from the start of treatment up to the 1-month follow-up visit

^9^At home: Daily with cumulative weekly measurements at 1, 2, and 3 weeks; bring to clinic at 1 month from the date of randomization

^10^Concomitant medications will be recorded as follows: All baseline medications will be recorded during treatment, and in the follow-up period, only pain medications will be collected. If the patient is hospitalized, only pain medications will be collected

^11^Please see Supplementary file 2: Appendix 5: Brief Pain Inventory (BPI)

^12^Please see Supplementary file 2: Appendix 6: The Functional Assessment of Cancer Therapy – General (FACT-G)

^13^Please see Supplementary file 2: Appendix 7: EuroQoL EQ-5D (HP)

**Table 3 Tab3:** Summary of assessments and data collection in the PROMISSED trial

Before treatment start	At 1 month post randomization	At 3, 6, 12, and 24 months post randomization
• FACT-G	• AE Assessment	• AE assessment
• BPI	• NPRS	• NPRS (required at 3 months)
• EQ-5D		• FACT-G
		• BPI
		• EQ-5D

An MRI or bone scan/CT of the spine is obtained for all participants at baseline and at 3, 6, 12, and 24 months after RT to evaluate the tumor response as well as the assess changes in vertebral bone, both subacute and long-term.

All participants in the upfront RT arm (arm 2) are evaluated for AEs according to CTCAE v5.0 and pain score using BPI short form once every five treatment days (typically at the time of their weekly on-treatment visit). Only participants in arm 2 (RT arm) are evaluated for radiation-related AE. In the event of an SRE, the following assessments will be attempted to be completed within 1 week. As it may not be feasible that the research team will be notified of all SREs within 1 week, or a participant may not be able to come to the institution, these assessments shall be considered optional but shall be endeavored for:Clinical examinationPerformance status assessmentImaging studiesAE evaluation (CTCAE v 5.0) for arm 2 participantsBPI Short FormEQ-5D-5L

For those participants that cannot come in for follow-up in-person visits or within 1 week of an SRE occurring, a telephonic assessment is considered sufficient, while clinical evaluation and imaging get postponed. Meanwhile, if the participant in this situation gets any of these assessments completed at another institution, efforts are made to obtain those records. If possible, the AE evaluation is also conducted through the telephonic assessment. If the participant in consideration is unable to complete Quality of Life Assessments, research staff are allowed to assist the patient. Furthermore, the BPI Short Form, the NPRS, and EQ-5D-5L in this case may be administered telephonically or directed to the patient through either postal mail, fax, or email by the physician, physician office assistant, or research staff. The mode of sending and receiving questionnaires is determined based on the participant’s preference. If participants cannot be reached through phone calls, the contact information on file will be used for a multipronged approach to get follow-up data.

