A Wilcoxon rank-sum test will be utilized to compare the number of hospitalizations secondary to SREs between the trial arms. For comparing the quality of life and pain level between the trial arms, we will assess at 3 months, 6 months, 12 months, and within 1 week of any SRE (optional). The individual and overall scores derived from the scales described previously will be summarized at these assessment points using means and standard deviations, or medians, and inter-quartile ranges. We will evaluate categorical variables from EQ-5D-5L between the trial arms using Fisher’s test at each time point as well, from which we will determine odds ratios with 95% confidence intervals. We will summarize other non-quantifiable answers (such as treatment received for pain control) in a descriptive fashion. For the score for pain interference on the BPI Short Form scale, we will consider it as the average of the seven interference questions as long as ≥ 4 questions are complete. The mean difference between the trial arms with regard to scores on these scales will be assessed for both statistical and clinical significance. This will be done using Wilcoxon rank-sum tests and established MCIDs. For scales lacking established MCIDs, the “half standard deviation” rule will be applied, wherein the differences of a half standard deviation in the scores between trial arms considered clinically meaningful. After the study is completed, we will plot data at each assessment point, including the number of trial participants in each arm, mean scale scores, and their trends over time. Based on this, we will consider utilizing more exhaustive regression analyses including generalized linear models. We will utilize log-rank tests to compare time-to-event endpoints such as PFS and OS. For toxicity, we will tabulate all AEs at 3, 6, 12, and 24 months post-randomizations in the early upfront RT arm.

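### The five-treatment-day interval for on-treatment AE and BPI checks does not fit three of the six RT schedules, and the planned AE table names no time point before 3 months

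*Protocol article*

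**What the plan says.** **On-treatment checks.** The text of the Schedule of assessments section has all arm 2 participants evaluated for AEs under CTCAE v5.0 and for "pain score using BPI short form once every five treatment days (typically at the time of their weekly on-treatment visit". In the same section, Table 2 marks AE evaluation under Treatment and at 1, 3, 6, 12 and 24 months. Its Treatment column has the numeric pain rating scale but no BPI.

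**RT schedules.** Under Study interventions, "A variety of dose fractionation schedules including conventional palliative doses as well as SRS schedules are allowed per protocol". Table 1 lists six, among them "2400 cGy 3 800 cGy", "2700 cGy 3 900 cGy", "2400 cGy 2 1200 cGy" and "3000 cGy 10 300 cGy". Each lesion is treated with one of the six.

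**Early follow-up.** Table 3 has a column headed "At 1 month post randomization" that includes an AE assessment. That visit has a window of 2 weeks either side and is timed from randomization.

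**Toxicity analysis.** The Planned statistical analysis section says "we will tabulate all AEs at 3, 6, 12, and 24 months post-randomizations in the early upfront RT arm". The Assessment of safety section adds that AEs judged definitely, probably or potentially related to protocol treatment are reported, with no time limit given.

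**The concern.** The checking interval suits conventional courses of one or two weeks. The protocol also allows courses of 2 or 3 fractions, and these carry the three largest doses per fraction. A site that takes the interval literally would make no on-treatment AE or BPI check for them, while Table 2 says there should be an AE evaluation. The schedule is chosen by the radiation oncologist, so any difference in how closely participants are watched would follow the schedule they received.

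The second mismatch is in reporting. The Study interventions section provides for medication for acute RT reactions, so early toxicity is foreseen. The two AE assessments nearest to RT are the two that the tabulation sentence leaves out. The Power calculation section states that RT is highly unlikely to bring more toxicity. A toxicity table that begins at 3 months, if it shows visit snapshots, would be poor evidence on that statement because early events that had resolved would not appear in it.

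**Working it through.** The plan gives no figure to reproduce. The check is a count from Table 1, followed by a comparison of scheduled and tabulated times.

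**Step 1: Table 1 is internally consistent.** Fractions × dose per fraction equals total dose in all six rows: 5 × 400 = 2000; 10 × 300 = 3000; 5 × 600 = 3000; 3 × 800 = 2400; 3 × 900 = 2700; 2 × 1200 = 2400 cGy.

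**Step 2: checks per single course under two readings of the interval.** Reading A puts the first check on the fifth treatment day: checks = fractions / 5, rounded down. Reading B allows one check in each block of up to five treatment days: checks = fractions / 5, rounded up.

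| Schedule | Gy per fraction | Reading A | Reading B |
|---|---|---|---|
| 30 Gy in 10 | 3 | 2 | 2 |
| 20 Gy in 5 | 4 | 1 | 1 |
| 30 Gy in 5 | 6 | 1 | 1 |
| 24 Gy in 3 | 8 | 0 | 1 |
| 27 Gy in 3 | 9 | 0 | 1 |
| 24 Gy in 2 | 12 | 0 | 1 |

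Reading A gives no check in three of six schedules. Reading B gives at least one in every schedule and agrees with Table 2's Treatment mark. The text does not choose between them.

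**Step 3: several lesions.** If lesions were treated one after another, a fifth treatment day would be reached with 2 lesions at 3 fractions each (6 days) or 3 lesions at 2 fractions each (6 days). The statistical section expects around 15% of participants to have multiple lesions, so this helps few of them.

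**Step 4: scheduled against tabulated AE times.**

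| Time | AE scheduled (Table 2) | Named for tabulation |
|---|---|---|
| Treatment | yes | no |
| 1 month | yes | no |
| 3 months | yes | yes |
| 6 months | yes | yes |
| 12 months | yes | yes |
| 24 months | yes | yes |

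Six times are scheduled and four are named. The two left out are the earliest.

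**Step 5: BPI.** The text requires an on-treatment BPI; Table 2 has none. The text also lists BPI among the assessments at the follow-up visits, 1 month included, while Tables 2 and 3 show none at 1 month. Anyone working from the tables would collect no BPI between baseline and 3 months.

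**The case against.** A reader might infer that acute toxicity of the short courses is neither captured nor reported. The documents do not support that, for these reasons:

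- Table 2 marks an AE evaluation under Treatment with no condition on fraction number, and the text covers all arm 2 participants. Reading B is natural, and the reference to weekly on-treatment visits may produce a check in a short course anyway.
- A 1-month AE assessment is scheduled for arm 2 under every schedule. Pain ratings run from the start of treatment to that visit, and supportive medication is documented.
- A table of all AEs at 3 months may be cumulative, in which case acute events fall in its first column. Related AEs are to be reported without a time limit, and the data safety and monitoring committee reviews AE data during the trial.

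All of this stands, and it limits the point to reconciling the passages. It does not remove it. Table 2 gives no timing for the Treatment evaluation, and the only text that does fits short courses badly. The 1-month visit falls roughly 2 to 6 weeks after randomization, and the article gives no interval from randomization to RT, so how well that visit covers the acute period is unknown. It is also one of the two times not named for tabulation. Nor is this merely detail left to an analysis plan: the article names specific tabulation times, and they differ from its own collection times.

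A second tempting step is to call for toxicity split by schedule. Arm 2 has about 74 / 2 = 37 participants, or about 37 / 6 ≈ 6 per schedule if evenly spread. No comparison between schedules is planned, and pooling them is not an error.

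**Conclusion.** The point holds as two mismatches that should be corrected. First, the on-treatment interval is not reached within a single course in 3 of 6 permitted schedules (8, 9 and 12 Gy per fraction) if counted to the fifth treatment day. It therefore needs to be reconciled with Table 2, which expects an on-treatment AE evaluation in every case and omits the BPI that the text requires. Second, 2 of the 6 scheduled AE times, treatment and 1 month, are not named in the tabulation rule.

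The size of the first depends on which reading of the interval the site uses; under the block reading no course lacks a check. The size of the second depends on whether the table is cumulative. If it is, early AEs are included. If it shows visit snapshots, early AEs that have resolved drop out. Neither mismatch affects the primary endpoint or the sample size.

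**What to change.** 1. In Schedule of assessments, reword the interval so that every course has at least one on-treatment CTCAE and BPI assessment, for example at the last fraction, with weekly assessments added for longer courses.
2. Mark BPI in the Treatment column of Table 2, and settle between the text and Tables 2 and 3 whether BPI is collected at 1 month.
3. In Planned statistical analysis, tabulate AEs for the treatment period and for 1 month as well as 3, 6, 12 and 24 months. Alternatively, state that the table gives the cumulative worst grade from the start of RT.

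The cost is one short form at a visit the participant already attends and two more columns in one table. Item 3 uses data already scheduled for collection, so it can apply to everyone enrolled. Items 1 and 2 can help only participants not yet treated when the change is made. No dose or treatment rule is affected.

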### Study endpoints

The endpoints selected in this trial have been utilized by similar trials [10, 14] and are defined within the time window from the date of randomization to death or 12 months, whichever occurs first. The primary endpoint of the study is the number of SREs per arm, which is defined as pathological fractures, spinal cord compression, or interventions (palliative RT, interventional procedures, or spine surgery) at 12 months. The secondary endpoints are as follows:Surrogates of health care cost, including the number and the duration of hospitalizations for SREsPain, as assessed using Brief Pain Inventory (BPI) short-form questionnaireHealth-related quality of life, as assessed using the Functional Assessment of Cancer Therapy-General (FACT-G) and the 5-level EuroQoL-5D (EQ-5D-5L)Median pain-free survival (PFS), defined as the time from study entry to the start of opioids or death. This definition has been utilized on basis of Rosen et al. [10]Median overall survival (OS), defined as the time from study entry to death or censoring due to follow-up

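### FACT-G has no remote-completion route for patients who cannot attend, and the prose visit list contradicts Tables 2 and 3 on FACT-G and on the 1-month visit

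*Protocol article*

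**What the plan says.** All references are to the Protocol article.

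- **Study endpoints** lists health-related quality of life as a secondary endpoint, "as assessed using the Functional Assessment of Cancer Therapy-General (FACT-G) and the 5-level EuroQoL-5D (EQ-5D-5L").
- **Schedule of assessments, opening:** "The full schedule of assessments is described in Table 2". Table 2 marks FACT-G at baseline and at 3, 6, 12 and 24 months. Table 3 has it before treatment and at the same four follow-up visits.
- **Schedule of assessments, prose visit list:** for the visits at 1, 3, 6, 12 and 24 months in both arms, it gives clinical evaluation, performance status, imaging, "evaluation of AE (CTCAE v5.0) for individuals in arm 2, BPI Short Form, and EQ-5D (Table 3"). FACT-G is not named.
- **Schedule of assessments, participants who cannot attend:** "For those participants that cannot come in for follow-up in-person visits or within 1 week of an SRE occurring, a telephonic assessment is considered sufficient". The instruments are then listed: "the BPI Short Form, the NPRS, and EQ-5D-5L in this case may be administered telephonically", with mail, fax and email as alternatives. FACT-G is again not named.
- **Same paragraph, on help with forms:** "If the participant in consideration is unable to complete Quality of Life Assessments, research staff are allowed to assist the patient".

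**The concern.** The remote rule is a list of named instruments, and it leaves out one that the trial has committed to analyse. Staff who follow it will telephone or mail three questionnaires and not the fourth.

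The participants concerned are not a random subset. The rule applies to people who cannot come in for follow-up, expressly including the week after an SRE. FACT-G would then be absent chiefly where health has worsened. Planned statistical analysis compares scale scores between arms by Wilcoxon rank-sum tests, with quality of life assessed at 3, 6 and 12 months. Such a test uses only participants who have a score, so the FACT-G result would describe those well enough to attend. The analysis plan may say how missing scores are handled, but no analysis can restore a form that was never offered.

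The second issue is that the prose and the tables give different instructions for the same visits, most plainly at 1 month.

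**Working it through.** The article states no figure on this point, so the check is a comparison of its own statements.

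**FACT-G, place by place**

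| Place in the article | FACT-G named? |
|---|---|
| Study endpoints | Yes |
| Table 2 (3, 6, 12, 24 months) | Yes |
| Table 3 (3, 6, 12, 24 months) | Yes |
| Prose visit list | No |
| List of assessments after an SRE (optional) | No |
| Remote-completion list | No |

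The omission from the prose visit list can be resolved, because the article calls Table 2 the full schedule and the prose list itself points to Table 3. The omission from the remote-completion list cannot be resolved that way. The tables say when FACT-G is due, not how it reaches someone who is not in clinic, and nothing else in the article gives it a telephone, mail, fax or email route.

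**What a non-attender yields under the rule as written:** BPI, NPRS and EQ-5D-5L can be completed; FACT-G cannot. One of the two quality-of-life instruments is lost and the other is kept.

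**The 1-month visit**

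| Item | Prose list | Tables 2 and 3 |
|---|---|---|
| Clinical evaluation | Yes | No |
| Performance status | Yes | No |
| Spine imaging | Yes | No |
| BPI | Yes | No |
| EQ-5D | Yes | No |
| NPRS | Not named | Yes |
| Adverse events | Yes, arm 2 | Yes |

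The imaging sentence after Table 3 gives baseline and 3, 6, 12 and 24 months, which agrees with Table 2 and not with the prose list. Scheduled scans within the 12-month endpoint window number 4 by the prose (1, 3, 6, 12) and 3 by Table 2 and the imaging sentence (3, 6, 12). The Abstract says that instruments are captured at 1 month without saying which. That fits either version, since NPRS is due then in both tables.

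**Size of the FACT-G loss.** Power calculation expects 60–80% of patients to be followed for at least 1 year, but does not split the remainder by reason or say how many visits would be remote. No loss can be derived from that figure.

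**The case against.** The best defence is that the omission is only a gap in wording. The remote sentence is permissive, staff may help with quality-of-life forms in general, and the article calls for several contact routes when telephone calls fail. Visit windows are also wide: ±4 weeks (28 days) at 3 months, ±8 at 6 and ±12 at 12. The article cites a mean inpatient stay of 18 days for the roughly one quarter of SREs that led to admission, so many temporary absences could end within the window. EQ-5D-5L covers quality of life remotely in any case.

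Much of this stands, and it limits the size of the point. It does not close the gap. Permission to assist says who may help, not that FACT-G may be sent out, and a list that names three of four questionnaires will naturally be read as leaving out the fourth.

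Three stronger readings are tempting but unsupported.

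- **A reader might infer that pain-free survival goes unmeasured.** It is "defined as the time from study entry to the start of opioids or death", and the Table 2 row for pain medication is marked only before enrollment. But footnote 10 to that row provides for pain medications to be collected in follow-up and during hospitalization, and the BPI also asks about their use. A start-date field is detail that a condensed article leaves to the full protocol.
- **A reader might infer that some sites would scan at 1 month and others would not.** The trial is single-center, the prose applies to both arms alike, and no differential effect on SRE detection is shown.
- **A reader might turn the planned SRE rates of 60% and 30% into a FACT-G loss by arm.** Those rates are per lesion, and the article does not say what share of patients with an SRE could not attend.

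**Conclusion.** The concern holds in a limited form and is minor. The remote-completion rule omits FACT-G, so FACT-G would be missing for participants who cannot attend and its comparison would favour those well enough to come in. This assumes that staff apply the list as written. That non-attenders are on average sicker is a reasonable inference from whom the rule covers, not a figure in the article. The extent of the loss is unknown. The quality-of-life endpoint is not left unmeasured, because EQ-5D-5L has a remote route.

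The conflict between the prose visit list and Tables 2 and 3 is a plain contradiction on FACT-G and on five items at 1 month. The two tables and the imaging sentence agree with one another, so the prose list is the odd one out. No effect on the primary endpoint or the sample size has been shown.

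**What to change.** 1. In Schedule of assessments, add FACT-G to the instruments that may be completed by telephone, mail, fax or email. The cost is one more 27-item questionnaire by a route already in use. The small downside is mixed modes of completion, already accepted for BPI and EQ-5D-5L.
2. Reconcile the prose visit list with Tables 2 and 3: name FACT-G at 3, 6, 12 and 24 months, and state one 1-month content in text and tables. Adopting the content of the tables would add no assessment to them. The reconciled list should also make clear whether adverse-event evaluation at that visit is for arm 2 only, as the prose says.
3. Optional tidying: align the pain-medication marks in Table 2 with footnote 10.

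These are wording changes and table marks only.
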